### Sample size

A sample of 1062 participants (354 in each arm) would give 80% power (alpha = 0.05, 2-tailed) to detect a difference of 10% in Pentavalent-3/PCV-3/Polio-3 vaccine coverage rate over the baseline expected coverage rate of 60%. For the same statistical parameters, a sample size of 1155 participants (385 in each arm) would detect a difference of 10% in Measles-1 vaccine coverage rate over the baseline expected coverage of 50%. A sample size of 1155 would give enough power to realise both objectives. The final sample size of 1446 infants (482 in each arm) was selected to allow for a potential dropout rate of 20% during the follow-up period.

### Recruitment and screening

Eligible Children (as identified through the eligibility criteria in the screening form) will be recruited at the participating immunization centers when they arrive for the BCG or Penta-1/PCV-1/OPV-1 vaccine as part of standard of care. Our study staff will be based at the centers to identify these children when they arrive at the centre. Our field workers will obtain consent for screening and then administer a short screening form to determine eligibility. The caregiver accompanying the child for the visit will provide information.

The entire study duration is 18 months and includes planning and actual field implementation. We expect to enroll study participants over a duration of approximately three to four months and follow up with them over the next 11 months. We have allocated approximately four months for enrolling/recruiting participants in the study. Preliminary data from our previous work in the study site indicates that on average there are 100 visits for BCG and Pentavalent-1/Polio-1/PCV-1 vaccine per center per month. Since we will be including 4 centers in our study, we would be able to recruit 1446 participants over a period of approximately three to four months.

### Informed consent

Among those children who are eligible for the study, their caregivers will be approached for enrolment into the study with a consent form informing them of the nature, rationale and anticipated risks and benefits of the study. The consent form will be in the local language and read out to the participants; those who agree to participate will be asked to sign/put their thumbprint on the form to signify their consent. They will be provided time to ask questions and think about their decision to participate during the process of obtaining consent. If the respondent agrees to participate in the study, he/she will be given an instruction card (post randomization) outlining the procedure to be followed in the (treatment or control) group that they have been allocated to, and will also be provided contact details for the relevant person to whom further questions can be directed. Subjects will not receive a copy of the consent form and no audio or video materials will be used during the consent process. At each follow-up visit, the field workers will ensure that participants understand and follow the protocols of the research.

### Participant withdrawal

In the event of participant withdrawal from the study due to withdrawing consent, the date and reason for withdrawal will be properly documented. If the participant was in either of the two treatment groups, they will be asked to return the bracelet. Data collected on participants before withdrawal will be retained but not included in the final analysis. Since this is a minimal risk study, we do not expect any discontinuation of interventions in response to harm caused by the bracelets.

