### Randomization

The randomization sequence will be generated by the PI in Stata version 13 with a 1:1:1 allocation, using random block sizes of 3, 6, 9 and 12. The allocation sequence will be concealed from the study staff responsible for screening and enrolling participants in sequentially numbered, opaque, sealed envelopes. After consent and randomization by the field staff, each child will be assigned a unique study ID (a sticker containing the study ID will be pasted on the child’s government issued EPI card). The field staff will sequentially enroll 1446 children from the four participating EPI centers over a period of approximately 3–4 months. Because of the nature of the intervention, neither the participants, nor the field staff enrolling the participants will be blinded during and post randomization.

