### Statistical methods

The baseline characteristics of the three groups will be compared by using the Student’s t-test for continuous variables and the chi-square test for categorical variables (using alpha = 0.05 for evaluating statistical significance). We will use intention to treat analysis—that is, all subjects will be analyzed with the assumption that they remained in the treatment group to which they were initially assigned.

$$ \mathsf{Y}=\mathsf{c}+\mathsf{i}.\left(\mathsf{allocation}\ \mathsf{group}\right)+\mathsf{\gamma X}+\mathsf{\varepsilon} $$

Y is the relevant outcome measure (for instance Pentavalent-3 coverage)

C is the constant that gives the value of the outcome for the control group

Allocation group is a categorical variable with 3 levels; “0-Control Group”, “1-Alma Sana Group”, “2-Simple Silicon Group”.

X is the set of possible covariates (gender, mother’s education etc.)

We will use the xi command to create these indicator variables and run the regression/model all in one command on STATA. Logistic regression will be used to determine whether the difference in outcome between the two treatment groups and control group are statistically significant and whether the difference in outcome between the two treatment groups is statistically significant. Multiple imputation will be used to handle missing data. The data will be analyzed in STATA version 15 (StataCorp. 2017. Stata Statistical Software: Release 15. College Station, TX: StataCorp LLC).

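### Children whose caregivers withdraw consent are left out of the final analysis, which contradicts the stated intention-to-treat analysis and can bias the coverage comparison in either direction

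*Protocol article*

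**What the plan says.** Two sections of the protocol article fix who enters the analysis.

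- **Participant withdrawal.** The rule is limited to one event: "In the event of participant withdrawal from the study due to withdrawing consent". For these children, "Data collected on participants before withdrawal will be retained but not included in the final analysis". One consequence applies to the bracelet arms only: "If the participant was in either of the two treatment groups, they will be asked to return the bracelet".
- **Statistical methods.** The analysis is called intention to treat, explained as "all subjects will be analyzed with the assumption that they remained in the treatment group to which they were initially assigned". The same section adds: "Multiple imputation will be used to handle missing data".

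Two other sections bear on the point. Randomization states that "neither the participants, nor the field staff enrolling the participants will be blinded during and post randomization". Data collection methods treats dropout from the vaccination schedule as an outcome and allows for contacting, towards the end of follow-up, caregivers who did not attend. A child who merely stops coming is therefore not withdrawn and stays in the analysis.

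**The concern.** A randomised child whose caregiver later withdraws consent is kept by one rule and removed by the other. The article defines no modified intention-to-treat set and no second analysis set that would let both stand. An analysis plan could follow only one of them.

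The removal happens after randomisation, in an open trial, and may be related to allocation. Only the bracelet arms are asked to keep an item on the child at all times and have it checked at each follow-up visit (Improving adherence). If withdrawal differs by arm, and withdrawn children differ from the rest in their chance of completing vaccination, the arms analysed are no longer the arms randomised. The coverage difference would then carry a selection component under an intention-to-treat label. If the conflict is left open, the choice between the rules could also be made after outcomes by arm are known.

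**Working it through.** **1. The plan's own figures.** Inputs from the Sample size section: 60% against 70% (Pentavalent-3/PCV-3/Polio-3), 50% against 60% (Measles-1), two-sided alpha 0.05, power 80%, dropout 20%. With the unpooled two-proportion formula, n = (1.960 + 0.842)² × [p1(1−p1) + p2(1−p2)] / d², where the squared term is 7.849:

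- 60% vs 70%: 7.849 × (0.24 + 0.21) / 0.01 = 353.2, so 354 per arm.
- 50% vs 60%: 7.849 × (0.25 + 0.24) / 0.01 = 384.6, so 385 per arm.
- Dropout: 385 / 0.8 = 481.25, so 482 per arm, and 3 × 482 = 1446.

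All stated figures reproduce. The 482 per arm is used below.

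**2. Effect of the exclusion when the bracelet does nothing.** Let p be true coverage (equal in the two arms compared), w the share withdrawn in an arm, and c coverage among withdrawn children. Analysed coverage in that arm is

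(p − w·c) / (1 − w).

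The spurious difference is this quantity for the bracelet arm minus that for control. The rejection probability is that of a two-sided 0.05 two-proportion z-test with 482(1 − w) children per arm (pooled standard error for the critical value, unpooled for the distribution under bias).

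The values of w and c are assumptions, because the article gives neither. The values of p are the expected rates in the Sample size section.

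Worked case, p = 60%, c = 0, withdrawal 10% vs 2%: bracelet 0.60/0.90 = 66.67% of 433.8 children; control 0.60/0.98 = 61.22% of 472.4. The difference is 5.44 points. The pooled standard error is 0.0320 and the unpooled 0.0319, giving a rejection probability of about 40%.

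| Withdrawal, bracelet vs control | p | c | Bracelet | Control | Difference (points) | Type I error |
|---|---|---|---|---|---|---|
| 5% vs 2% | 50% | 0% | 52.63% | 51.02% | +1.6 | 8% |
| 5% vs 2% | 50% | 20% | 51.58% | 50.61% | +1.0 | 6% |
| 5% vs 2% | 60% | 0% | 63.16% | 61.22% | +1.9 | 9% |
| 5% vs 2% | 60% | 20% | 62.11% | 60.82% | +1.3 | 7% |
| 10% vs 2% | 50% | 0% | 55.56% | 51.02% | +4.5 | 28% |
| 10% vs 2% | 50% | 20% | 53.33% | 50.61% | +2.7 | 13% |
| 10% vs 2% | 60% | 0% | 66.67% | 61.22% | +5.4 | 40% |
| 10% vs 2% | 60% | 20% | 64.44% | 60.82% | +3.6 | 20% |

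Differences were taken before rounding.

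**3. Where the bias is small, absent or reversed** (same p and c ranges).

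- 2% vs 1%: +0.3 to +0.6 points, type I error 5.1-5.4%.
- 10% vs 10% with the same c in both arms: difference 0, type I error 5%.
- c equal to p: difference 0 whatever the withdrawal shares.
- 2% in the bracelet arm vs 5% in control: −1.0 to −1.9 points, that is, against the bracelet.

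**The case against.** The strongest reply is that the rule is narrow and its effect probably small. It applies to withdrawal of consent, not to missed visits. The article describes a minimal-risk study whose immunization data are copied from the routine EPI card, so few caregivers may withdraw. A caregiver who dislikes the bracelet can leave it off and remain in the analysis: wearing is observed as adherence, and dislikes are asked about in the closing interview. The bracelet is requested back only after withdrawal, so its return is a consequence and not a cause. All of this stands. It limits the size of the problem but does not remove the contradiction.

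It also rules out three stronger readings that a reader might infer.

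- *The 20% dropout allowance is the share removed.* It is not. That figure is overall dropout, and schedule dropout stays in as an outcome.
- *The analysis is in effect per-protocol.* It is not, because non-wearers and schedule drop-outs remain. It is intention to treat minus consent withdrawals.
- *The rule favours the bracelet.* Nothing in the article fixes the direction. Differential withdrawal is plausible, but no rate is given for any arm.

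It may also be said that consent could forbid using the data. The consent form is not shown, so this cannot be settled here. The article does say that the earlier data are kept, and gives no reason for leaving them out of the analysis.

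**Conclusion.** The contradiction is established by the text alone and holds at any withdrawal rate: the final analysis cannot both include all subjects as assigned and leave out those who withdraw consent. As written, the primary comparison would use a modified intention-to-treat set under the name intention to treat.

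The size of any bias is conditional. With no true effect and 482 randomised per arm, it runs from well under one point at 2% vs 1% withdrawal to 5.4 points at 10% vs 2%, against a design difference of 10 points. The upper figures need both a large imbalance in consent withdrawal and very low coverage among withdrawn children, and the article supports neither assumption. A claim that the rule will produce a false bracelet effect would go too far. What can be said is that it allows a bias of unknown sign, and that the bias is avoidable to the extent that outcomes are recorded before withdrawal or validly imputed.

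**What to change.** Replace the sentence in Participant withdrawal that leaves these data out with wording such as:

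> All randomised children are included in the primary analysis in their allocated group. Data collected up to withdrawal are used where consent allows, including doses already recorded. Outcomes not observed after withdrawal are handled by the planned multiple imputation, with a sensitivity analysis counting withdrawn children as not vaccinated for doses not already recorded. Withdrawals are reported by arm.

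An analysis without the withdrawn children may be kept as a sensitivity analysis, labelled as such.

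No register or other follow-up after withdrawal is needed, and none should be implied: that would be new data collection on families who have withdrawn. The planned 482 per arm does not change. The cost is a protocol change, which under Protocol modifications goes to both review boards, and slightly more analysis work. One limit remains. Pentavalent-3 and Measles-1 fall late in follow-up, so many withdrawn children will have no recorded outcome. The result for them will rest on the imputation model, which is why the sensitivity analysis and the counts by arm are needed.

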### Randomization

The randomization sequence will be generated by the PI in Stata version 13 with a 1:1:1 allocation, using random block sizes of 3, 6, 9 and 12. The allocation sequence will be concealed from the study staff responsible for screening and enrolling participants in sequentially numbered, opaque, sealed envelopes. After consent and randomization by the field staff, each child will be assigned a unique study ID (a sticker containing the study ID will be pasted on the child’s government issued EPI card). The field staff will sequentially enroll 1446 children from the four participating EPI centers over a period of approximately 3–4 months. Because of the nature of the intervention, neither the participants, nor the field staff enrolling the participants will be blinded during and post randomization.

### Interventions

#### Intervention a; Alma Sana bracelet

A vaccine reminder and tracker bracelet developed by Alma Sana Inc., a 501(c)3 non-profit organization founded in Indianapolis, Indiana, US, will be adapted for use in Pakistan (based on feedback received during the formative phase of the study). Children in intervention Group A will receive these bracelets. The bracelet uses a combination of symbols and numbers to denote the entire vaccine schedule a child is supposed to receive before the age of 2 years. Shapes indicate vaccines, and numbers signify the child’s age (Fig. 2). Additionally, mothers will be provided instructions on how to decode and use the bracelet. Every time a child receives a vaccine, vaccinators will use hole punchers to perforate shapes denoting the particular vaccine a child has received. Mothers can, therefore, look at the bracelet and know which vaccines her child has received and the dates of future visits. The bracelets will be manufactured in 2 different sizes to ensure they fit the child’s wrist as he/she grows older.

**Fig. 2 Fig2:**
[figure not shown]
Adapted version of Alma Sana Bracelet (for Pakistan)

#### Intervention B; simple silicone bracelet

This is a simple silicone bracelet used by Interactive Research and Development in a previous project. Children in intervention Group B will receive these bracelets. This bracelet has six symbols to remind parents that their child needs to make six distinct vaccination visits before he reaches 2 years of age. The first five symbols are represented by a crescent shape and the sixth symbol is represented by a star shape to denote that the child is fully immunized (Fig. 3). At the time of enrolment, mothers will be provided instructions on how to decode and use the bracelet. Every time a child receives a vaccine, vaccinators will use hole punchers to perforate shapes denoting the particular vaccine a child has received. These bracelets will be manufactured in 2 different sizes and colors (pink for baby girls and blue for baby boys).

**Fig. 3 Fig3:**
[figure not shown]
Simple Silicone Bracelets

All participants (irrespective of whether they are in the intervention group A or B or control group) will receive the routine EPI vaccinations as per Pakistan’s EPI Immunization schedule (one dose of BCG and Polio soon after birth, 3 doses of Pentavalent/Polio/PCV at 6, 10 and 14 weeks, and 2 doses of Measles vaccine and 9 and 15 months of age) and the vaccinator will record the child’s immunization data in the EPI immunization card as well as EPI register. The difference between the intervention and standard care is only the provision of bracelets. The comparator group will only receive the standard care.

#### Improving adherence

To ensure that participants adhere to the interventions, the study team will ensure at the time of enrolment and at each follow-up visit, that participants are aware of the purpose of the bracelet, how to use it and the importance of making their child wear it at all times. Additionally, at each follow up visit, the participants will be observed for whether their child is wearing the bracelet or not and will be asked if they have any questions regarding the bracelet.

### Outcomes

The key study outcomes and their associated measurement is outlined in Table 1 below.

**Table 1 Tab1:** Outcome Indicators and Measurement

Outcome of Interest	Measured by
At least 10% increase in Pentavalent-3/PCV-3/Polio-3, Measles-1 coverage. Indicators:	Enrolment and follow-up immunization visits.
1. % children vaccinated (on time), by antigen	
2. % of children fully vaccinated	
3. Drop-out rate	
Improved understanding of bracelet use:	Detailed feedback questionnaire
1. Reasons for delayed immunizations	
2. Reasons for dropping out	
3. Do bracelets influence the decision of parents to visit immunization centers on time?	

### Data collection methods

At the child’s first visit to the center, the field worker will use an Enrolment Form to note the name and age of the child along with the immunizations received during the visit in addition to basic demographic information.

For the follow-up visits by the caregivers to get the subsequent vaccinations (3–4 visits), our field workers will be based at the participating EPI centers throughout the follow-up period. The field workers will use the unique study IDs to identify study participants when they come for follow-up visits. At each follow-up visit, the field worker will record the vaccine administered, and date of administration for each child enrolled in the study, including verifying data on past immunizations and due vaccines. Therefore, for each study participant, the field workers will collect data 3–4 times during the follow-up period.

After the completion of the follow-up phase, short (15–20 min) phone or in-person interviews will be conducted to collect follow up vaccination data (if missing) and data on experiences of study participants regarding the bracelets. Dropout from the vaccination schedule is also an outcome. We will be able to identify the caregivers who did not show up for the follow up phase, these participants may be contacted through phone or in person visits towards the end of the follow up period. Key data points to be collected will include reasons for drop-outs, whether mothers understood how to use the bracelets, how often mothers said their babies wore the bracelets and why, what mothers liked and disliked about the bracelets and whether mothers would continue using the bracelets as reminders moving forward.

At all points of the study, data will be collected directly from participants using paper-based questionnaires. Immunization data is copied from the child’s government-issued EPI card. All data will be transferred to a secure electronic medium on a daily basis.

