Currently, immunization cards are used as a systemized way to record and track vaccinations. However, since cardholder prevalence is < 70% in 21 of 33 least developed countries [14] these cards provide an inaccurate coverage estimate and fail to empower mothers who are unable to read and understand the cards. With the recent proliferation of technology and mobile phones, mHealth, particularly digital registries and SMS reminders provide a promising avenue to improve vaccination coverage. However, evidence for such interventions is mixed and limited [15], particularly when taking into account the fact that the majority of unvaccinated children are concentrated in a small number of countries which do not always have the necessary preconditions for mHealth interventions to succeed [16]. Evidence from studies in Pakistan show low response rates to vaccine oriented SMS reminders as well as no impact on self-reported medication adherence for TB. Some of the main barriers limiting the efficacy of mHealth interventions include inability of caregivers to read the messages [17], frequent changing of phone numbers [17, 18] as well as low phone ownership [19] and literacy rates among women who are most often the primary caretakers and responsible for bringing children for immunization. As an alternate to both paper based and technology based reminders, silicone vaccine reminder bracelets are relatively simple and cheap to use without the need for complicated infrastructure and resources. They make use of numbers and symbols to convey the vaccination schedule and immunization status of the child and therefore have the unique benefit of being suitable for illiterate or less educated mothers. Additionally, they can be adapted to most local settings regardless of the spoken language and infrastructure availability; input from vaccinators and mothers can be used to customize the bracelets to meet the needs and preferences of the communities they are introduced in, giving them an advantage over other home-based reminders. Furthermore, these bracelets are simple to use, inexpensive, and baby-safe.

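### Vaccination outcomes rest on a family-held card and inconsistently worded tracing, while only two arms carry a visible study item, so ascertainment can differ by arm

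*Protocol article*

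**What the plan says.** **Identifier.** Under Randomization, "a sticker containing the study ID will be pasted on the" child's EPI card, in all arms. Under Data collection methods, "The field workers will use the unique study IDs to identify study participants when they come for follow-up visits".

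**Source of outcome data.** Data collection methods has immunization data copied from the EPI card. Table 1 measures coverage from enrolment and follow-up visits. At each follow-up visit the field worker also verifies earlier doses.

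**Recovery of missing data.** The same section says that short interviews will be held after follow-up, both to obtain missing vaccination data and to ask about experience with the bracelets. A few lines later, on caregivers who did not come to follow-up, it says "these participants may be contacted through phone or in person visits towards the end of the follow up period".

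**What differs by arm.** Groups A and B wear a bracelet in which a hole is punched for each vaccine. The Abstract assigns the punching to study staff; the Interventions section assigns it to vaccinators. Under Improving adherence, the study team looks for the bracelet at each follow-up visit and invites questions about it. Controls have no counterpart.

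**Blinding.** Participants and the field staff who enrol them are unblinded (Randomization).

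**The other record.** For every child the vaccinator enters "immunization data in the EPI immunization card as well as EPI register" (Interventions). The register is not named as a source of outcome data.

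**The protocol's view of cards.** The Background reports that "cardholder prevalence is < 70% in 21 of 33 least developed countries" and regards cards as an unreliable basis for estimating coverage.

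**The concern.** The identifier and the outcome record sit on the same piece of paper, which the family must bring. A child who attends without it may not be recognised as a participant, and the dose may not be captured that day. In a bracelet arm, a punched silicone band on the wrist can alert staff that this is a study child, and it can help the caregiver recall doses at interview. A control child offers no such cue.

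A visit missed in this way looks the same as a drop-out, so it falls where the tracing wording is weakest. When the interview takes place, bracelet questions in the same conversation make the allocation evident while vaccination status is being established.

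If capture differs by arm, the recorded coverage difference mixes the effect of the bracelet with the effect of recording. This touches both primary comparisons (A and B against control). Intention-to-treat analysis does not remove it. Nor does multiple imputation, if an uncaptured dose is scored as not vaccinated or if capture depends on both arm and outcome.

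**Working it through.** **1. The plan's own figures.** The plan states that its samples "would give 80% power (alpha = 0.05, 2-tailed"), for 60% against 70% (Penta-3/PCV-3/Polio-3) and 50% against 60% (Measles-1). With the unpooled normal formula, n = (1.96 + 0.8416)² × [p₁(1−p₁) + p₂(1−p₂)] / 0.10²:

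- 60% vs 70%: 7.849 × (0.24 + 0.21) / 0.01 = 353.2, so 354 per arm.
- 50% vs 60%: 7.849 × (0.25 + 0.24) / 0.01 = 384.6, so 385 per arm.
- Dropout of 20%: 385 / 0.80 = 481.25, so 482 per arm and 3 × 482 = 1446.

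All three reproduce. The point contests no stated figure.

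**2. What unequal capture would do.** Let p be true coverage, equal in both arms (no true effect), and let s_C and s_B be the probabilities that a dose actually given is recorded in control and in a bracelet arm. An unrecorded dose is scored as not vaccinated. Then

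spurious difference = p × (s_B − s_C).

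The documents give no capture probabilities. Every s below is an assumption.

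Worked case with p = 0.60, s_C = 0.90, s_B = 0.95 and 482 per arm:

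- Recorded coverage is 0.54 and 0.57; the difference is 0.03.
- Pooled standard error under the null: √(2 × 0.555 × 0.445 / 482) = 0.0320.
- Unpooled standard error: √((0.54 × 0.46 + 0.57 × 0.43) / 482) = 0.0320.
- Rejection probability: 1 − Φ((1.96 × 0.0320 − 0.03) / 0.0320) + Φ((−1.96 × 0.0320 − 0.03) / 0.0320) = 0.153 + 0.002 = 0.155.

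The same calculation over a range, one bracelet arm against control, 482 per arm:

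| Assumed capture, control / bracelet | Spurious gap at 60% | Type I error | Spurious gap at 50% | Type I error |
|---|---|---|---|---|
| equal | 0 | 5% | 0 | 5% |
| 95% / 97% | 1.2 points | 6.6% | 1.0 points | 6.1% |
| 90% / 95% | 3.0 points | 15.5% | 2.5 points | 12.2% |
| 85% / 95% | 6.0 points | 46.4% | 5.0 points | 34.5% |
| 80% / 95% | 9.0 points | 80.0% | 7.5 points | 65.1% |

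Swapping the two capture rates gives the same sizes with the sign reversed, against the bracelets.

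The capture gap that would by itself produce the whole 10-point target difference is 0.10 / 0.60 = 16.7 percentage points at 60% coverage and 0.10 / 0.50 = 20 points at 50%.

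Equal but incomplete capture creates no false difference. It shrinks a true one: at 90% capture in both arms, a true 10-point gain is recorded as 0.90 × 10 = 9 points.

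**3. The two tracing statements side by side.** One sentence commits to interviews where vaccination data are missing; another makes contact with non-attenders discretionary. A non-attender is, by definition, someone whose later vaccination data are missing. The two statements therefore cover overlapping children with different force. Neither gives a rule tied to arm-independent criteria.

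**The case against.** A reader might infer that the bracelet serves as a study identifier and a second dose record in two arms, so that the trial is biased in favour of the intervention. The documents do not support that.

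- **Written procedure.** Identification by study ID and copying from the card apply identically to all arms. The punched holes inform caregivers and are nowhere described as outcome data. Any influence would be indirect.
- **Direction.** A caregiver who relies on the bracelet might leave the card at home, and the bracelet arms would then be under-recorded. Non-wear, which the protocol anticipates, would weaken any cue.
- **Safeguards.** Interviews for missing vaccination data are promised, so recovery is not simply optional. A Penta-3 dose missed on the day can be picked up when earlier doses are verified at a later visit. Name and age are recorded at enrolment, and field workers stay at the centres.
- **Card retention.** The Background figure concerns cardholder prevalence across least developed countries. It is not a loss rate in this cohort, whose cards were in hand at enrolment.
- **Blinding.** Only the enrolling staff are said to be unblinded; the interviewers are not specified.
- **Condensed article.** Details such as the number of contact attempts may be in the full protocol.

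Most of this stands and limits the point to a risk. It does not remove the risk. The article itself fixes the identifier, the source and the discretionary wording. Later verification cannot help Measles-1, the last dose followed, before the interview. Verification and interview still depend on the card or on recall.

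**Conclusion.** The point holds as a risk of differential ascertainment under nominally equal procedures. It is not a demonstrated bias in favour of the bracelets. Three features create the risk together: identification and outcome data both depend on the family-held card, tracing of non-attenders is worded inconsistently, and only two arms carry a visible, staff-checked item that is discussed in the same interview as vaccination status.

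The size is unknown. The illustrations rest on assumed capture rates, no true effect, and uncaptured doses scored as not vaccinated. They run from negligible (about 1 point and 6–7% type I error for a 2-point capture gap) to serious (5–6 points and 34–46% for a 10-point gap). The Background figure on cards cannot be used to choose among them. Since a modest imbalance could matter and the remedy is cheap, the change should be made.

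**What to change.** Amend Data collection methods as follows.

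1. **One tracing rule.** Reconcile the two statements so that every child in any arm without a Penta-3/PCV-3/Polio-3 or Measles-1 record *will be* traced, by the same rule and with the same number of attempts. Where possible, the caller works from a list that does not show allocation.
2. **Order of questions.** Record vaccination status before any question about the bracelet. Do not count bracelet perforations as evidence of a dose.
3. **Register cross-check.** For all three arms, search the EPI registers of the four centres, matched on details collected at enrolment, as an additional outcome source. Count a dose documented in either the card or the register. The register should supplement the card, not replace it, because the four centres' registers would miss doses given elsewhere.

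The cost is some extra abstraction time for field workers already stationed at the centres, plus wording. The interviews are already planned. The register search can be done retrospectively, so it remains possible although recruitment is complete.
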